#### Health-Related Quality of Life

Health-related quality of life is self-assessed by the Kinder Lebensqualitätsfragebogen (KINDL) questionnaire. The KINDL is a generic instrument for assessing health-related quality of life in children and adolescents. For study participants younger than 14 years, the KINDL child version is used, and for study participants 14 years and older, the KINDL adolescent version is used. The KINDL is a short, methodologically tested, and flexible measurement instrument consisting of 24 questions on the 6 domains of body/physis, feelings/psychology, self-assessment, family, friends, and school [21].

### Statistical Methods

The data analysis will involve both descriptive and analytical analyses. Initially, descriptive analysis will focus on the sociodemographic characteristics of the study population. Normal distribution of the data will be tested with the Shapiro-Wilk test. In terms of dropouts, intention-to-treat analysis will be performed using multiple imputations, to be able to calculate with a complete data set. To capture the longitudinal development of the activity level throughout the study period, a linear mixed model will be used to compare the change of the PA behavior over time between IG and CG. To investigate differences between the groups in activity-related self-efficacy, health-related quality of life, and PA enjoyment, these will be compared with 2-tailed *t* test or Mann-Whitney *U* test as appropriate depending on the distribution of the data. All analyses will be performed with RStudio (version 4.1.2; RStudio Team), with the level of significance set to 2-sided *P* values <.05 for all tests. RStudio was used for its tailored integration with the R programming language, providing an efficient and organized environment for reproducible data analysis, visualization, and documentation in our scientific study.

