### Phase-II Evaluation

#### Overview

After the implementation of the results of the first evaluation phase, the second evaluation in the form of an RCT will be conducted. The IG will use the KIJANI app in their everyday life over a period of 2 weeks, while the CG sticks to their normal everyday life without using the KIJANI app. Randomization will be 2:1 into IG and CG, with the randomization process clustered by age and gender to ensure equal distribution in the groups. The phase-II evaluation sample size was calculated with G*power (2-sided α of 0.05, power 0.9). A sample of 62 participants is planned for this study. Of these, 41 participants will be assigned to the IG and 21 participants will be assigned to the CG. After completion of the study, the CG will also have the opportunity to use the KIJANI app.

The primary outcome of the phase-II evaluation is the everyday PA of the children and adolescents. PA is objectively recorded in the form of daily step count via accelerometers integrated into the smartphone over the entire study period in IG and CG. Through the KIJANI intervention, we hope to increase the PA of children and adolescents by 10%.

Secondary end points are health-related quality of life, activity-related self-efficacy, PA enjoyment, as well as the user experience with the app. The last 3 will be investigated as described above in the phase-I evaluation. Secondary end points will be assessed before and after the intervention period.

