## Discussion

### Principal Findings

KIJANI is a mobile game explicitly developed for PA promotion in children and adolescents with a special focus on creativity as well as PA in the outdoor setting. The objective of the KIJANI intervention is to increase everyday PA in adolescents through a digital intervention approach using gamification and augmented reality. This study protocol describes the KIJANI intervention in detail, as well as the evaluation approach.

Even though activity promotion is highly indicated in adolescents, this young target group is difficult to reach, and adherence to intervention approaches, especially over the long term, is mostly rather low [22].

Several previous studies have assessed the effectiveness of mobile health approaches to increase PA in healthy adolescents. A systematic review on the effects of mobile health to increase PA concluded that mobile devices and apps may be an effective strategy for promoting PA in adolescents as they have high technology use. However, overall, there is only a small number of studies; a lack of RCTs; and a high risk of bias in this research sector, mostly including self-reported measures with the risk for recall as well as report bias [23]. Another systematic review on the quality and features of apps to improve PA, sedentary behavior, and diet also reported that generally, very few apps are available that specifically target children and adolescents and app quality was only moderate [24]. Overall, there is a need for high-quality app-based activity promotion approaches especially in children and adolescents.

Some previous studies have assessed the effects of digital gamification approaches on activity promotion. A meta-analysis revealed that the popular mobile augmented reality game “Pokémon Go” was associated with a significant increase in the users’ daily step count. In the game, participants are required to travel to different locations to capture virtual characters. Even though the game was not primarily designed to promote PA, it has reached masses of users and has shown to have the potential to influence their health behavior at least in the short term [25]. Long-term results are rare, but it seems that the novelty effect tends to wear off with time, and after 3 months, 80% of players stopped using the app [26].

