### Limitations

Several limitations should be considered when discussing this study protocol. In the phase-I evaluation, one-on-one interviews carry the risk of social desirability bias, where participants may provide responses perceived as socially acceptable rather than expressing their true opinions or behaviors. The phase-II evaluation carries the risk of the Hawthorn effect, which implies the awareness of being observed and studied that impacts people’s behavior. Based on this effect, PA levels might be higher than normal throughout the measurement period of 2 weeks.

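### The named primary comparison, change in steps over time within the two weeks of app use, tests whether trajectories differ and not whether activity is 10% higher

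*Protocol article*

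**What the plan says.** The Overview of the Phase-II Evaluation sets out the exposure: "The IG will use the KIJANI app in their everyday life over a period of 2 weeks", while the control group carries on as usual. The primary outcome is everyday activity, measured as daily steps from the smartphone's accelerometer across the whole study period in both arms. The aim is put as a level: "we hope to increase the PA of children and adolescents by 10" percent.

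The same section states assessment before and after the intervention only for the secondary end points. The Limitations warn that "PA levels might be higher than normal throughout the measurement period of 2 weeks", which gives step recording the same length as app use.

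The Statistical Methods name one analysis for the primary outcome: "a linear mixed model will be used to compare the change of the PA behavior over time between IG and CG". They do not say how time is coded, which coefficient is the primary test, or whether a group term will be interpreted.

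**The concern.** If steps are recorded only while the intervention group has the app, there is no earlier level from which change can be measured. Change over time compared between arms is then a group-by-time interaction within the treated period. It shows whether the gap between the arms widens or narrows from day 1 to day 14, and says nothing about the size of the gap itself.

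A randomised trial of a gamified app could well see its effect at once. If that effect holds, the interaction is null although the app worked. If it starts high and falls away, the interaction is negative although total activity rose. In either case the primary result would not answer the question about a 10% increase.

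**Working it through.** **1. The plan's own figure.** The Overview gives "2-sided α of 0.05, power 0.9", "A sample of 62 participants is planned for this study" and "41 participants will be assigned to the IG and 21 participants will be assigned to the CG". The split fits 2:1 (62 × 2/3 = 41.3). The total cannot be reproduced, because no effect size, SD or correlation is given. Solved backwards by the normal approximation, 90% power at 41 and 21 needs

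d = (1.960 + 1.282) × √(1/41 + 1/21) = 3.242 × 0.2683 = 0.87 (0.88 with the t distribution).

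If 10% were that effect, the coefficient of variation (CV) of a child's step count would have to be 0.10/0.87 = 11.5%. A within-between interaction with f = 0.21, two measurements and correlation 0.5 also gives 62. Neither set of inputs is in the article, so the sample size does not show which contrast was meant.

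**2. What a group-by-time contrast estimates.** Let Δ(t) be the expected difference in steps between the arms on day t, for t = 1 to 14. Any group-by-time contrast has the form Σ c(t)Δ(t) with Σ c(t) = 0. If Δ(t) = δ on every day, the contrast is δ × Σ c(t) = 0. This holds for linear day, week 1 against week 2, or 14 separate days, and for any variance. Power therefore equals alpha, 0.05.

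**3. Size under assumed variances.** The article gives no SD. I assume a mean of 10,000 steps a day, between-child CV of 10 to 40%, day-to-day CV of 30 to 50%, a random-intercept model, 14 complete days, and 41 and 21 children. With k = 1/41 + 1/21 = 0.07201:

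- Mean-level difference: SE = √{k(σ_b² + σ_w²/14)}.
- Linear slope difference: SE = √{k σ_w²/227.5}, since Σ(t − 7.5)² = 14 × 195/12 = 227.5.
- Mean level adjusted for an assumed 7-day baseline: replace σ_b² + σ_w²/14 by σ_b² + σ_w²/14 − σ_b⁴/(σ_b² + σ_w²/7).
- Power ≈ Φ(effect/SE − 1.96), plus the small opposite tail.

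Example at between/within CV of 20%/30% (σ_b = 2000, σ_w = 3000). The level SE is √(0.07201 × 4,642,857) = 578. For 1000 steps the ratio is 1.73 and power is Φ(−0.23) = 0.41. The slope SE is √(0.07201 × 9,000,000/227.5) = 53.4. A build-up from 0 to 20% has slope 2000/13 = 153.8 steps per day, so the ratio is 2.88 and power is Φ(0.92) = 0.82.

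| CV between / within | Constant +10%: group-by-time | Constant +10%: mean level | Constant +10%: mean level, 7-day baseline | Build-up 0 to 20%: group-by-time |
|---|---|---|---|---|
| 10% / 30% | 0.05 | 0.83 | 0.92 | 0.82 |
| 20% / 30% | 0.05 | 0.41 | 0.83 | 0.82 |
| 30% / 40% | 0.05 | 0.22 | 0.58 | 0.58 |
| 40% / 50% | 0.05 | 0.14 | 0.40 | 0.41 |

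A fade from 20% to 0 also averages +10%. Its slope difference is −153.8 steps per day, and it is significant as often as the build-up (0.41 to 0.82) but with the opposite sign. A build-up from 0 to only 10% gives group-by-time power of 0.30, 0.30, 0.19 and 0.14.

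**4. Simulation check.** Mixed models fitted to 300 simulated trials at 20%/30%, some with convergence warnings, rejected for a constant +10% in 6% (interaction) and 38% (group term). For the 0 to 20% build-up the interaction rejected in 83%. A second simulation used 4000 trials per scenario, mean 8000, between-child CV 30% and day SD 3000. At a constant +30% the slope test rejected in 5.0% and the mean-level test in 93%; at +10% the figures were 5.2% and 21%.

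**The case against.** The strongest reply is that the sentence in the Statistical Methods does not fix a slope test. Coding of time and choice of coefficient are commonly left to an analysis plan, and a mixed model normally also yields a group term that estimates level. That is fair as far as it goes. But the article does name a comparison, change over time between arms, and step 2 shows that no coding of time rescues it for a constant effect. A faithful analysis plan would carry the mismatch forward.

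Second, the lack of baseline steps is inferred. It rests on the 2-week measurement period in the Limitations and on before-and-after assessment being stated only for secondary end points. The article never says outright that no earlier steps are recorded. This stands. If a baseline exists, change from it compared between arms is a sound contrast, and the defect shrinks to not having said so.

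Third, a reader might infer that the trial cannot detect a 10% increase at all. The documents do not support that: a gradual build-up averaging 10% is detectable by the interaction, with power 0.41 to 0.82.

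Fourth, a reader might infer that the protocol predicts fading within the trial. The remark "it seems that the novelty effect tends to wear off with time" in the Principal Findings concerns another augmented-reality game and is tied to a 3-month figure. Fading within 14 days is a possibility and not the protocol's forecast.

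Fifth, the mean-level contrast is itself weak at 10% under most of the assumed variances. This also stands and is carried into the fix.

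**Conclusion.** The point holds as a mismatch between the stated aim and the named primary comparison. If steps are recorded only during the 2 weeks of app use, an immediate and sustained uplift has an expected group-by-time contrast of zero. That result is algebraic and needs no variance assumption, only a difference in steps that is the same on each day. A fading effect would give a negative contrast with higher mean steps, and a gradual build-up could be found. All other power figures rest on my assumed mean, CVs, random-intercept structure and complete data. The inference that there is no baseline is well supported by the text but not stated in it.

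**What to change.** Define the primary contrast in the Statistical Methods or the analysis plan as the difference between intervention and control in mean daily steps over the 2 intervention weeks. Estimate it from the mixed model with a random participant intercept and express it also as a percentage of the control mean. Specify it as the difference averaged over days: if a group-by-time term is in the model, the bare group coefficient is the difference at whichever day is coded zero.

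State whether steps before the intervention are recorded. If they are, define the baseline period, adjust the primary contrast for it, and define change relative to it. Report group-by-time, for example week 1 against week 2, as a secondary description of build-up or fading.

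The cost is a few sentences and no extra data, settled before phase-II data are seen. The downside is power: without a baseline the mean-level contrast has about 0.14 to 0.83 for a 10% effect under the assumed CVs, against 0.40 to 0.92 with an assumed 7-day baseline. The sample size statement should therefore give the SD and the contrast on which the 62 rests.

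### Three secondary end points are measured before and after the intervention but compared without baseline adjustment, by a test that the data choose

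*Protocol article*

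**What the plan says.** The Phase-II Evaluation overview in the protocol article states "Secondary end points will be assessed before and after the intervention period". It randomises 2:1, organised by age and gender: "41 participants will be assigned to the IG and 21 participants will be assigned to the CG".

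Statistical Methods then fixes the analysis of three of these end points as a t test or a Mann-Whitney U test, according to how the data are distributed: "To investigate differences between the groups in activity-related self-efficacy, health-related quality of life, and PA enjoyment, these will be compared with 2-tailed". The stated distribution check is "Normal distribution of the data will be tested with the Shapiro-Wilk test". For dropouts, "intention-to-treat analysis will be performed using multiple imputations". All tests are carried out "with the level of significance set to 2-sided" P values below .05.

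The linear mixed model in the same section is stated for physical activity only. For the three questionnaires no covariate is named, and the compared quantity (post score or pre-post change) is not given.

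**The concern.** A baseline value of each questionnaire will be on file for participants in both arms. Over two weeks it should predict the follow-up value, so a model that adjusts for it gives a tighter estimate of the group difference. The named two-sample tests cannot adjust for it, nor for age and gender, which the randomisation uses. With 21 controls, precision is scarce.

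The second issue is what gets reported. A t test addresses a difference in means; Mann-Whitney U addresses the ordering of the two arms. If the observed distribution selects the test, the effect measure is not fixed in advance, and the three end points could be reported on different scales. The plan also intends multiple imputation, for which a mean difference with its standard error is the natural input.

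At stake are the precision and interpretability of three secondary comparisons.

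**Working it through.** **Inputs from the protocol article.** Arms of 41 and 21; "2-sided α of 0.05, power 0.9"; pre and post assessment of the secondary end points; a t test or Mann-Whitney U test without covariates.

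**Assumptions, not in the document.** Pre-post correlation r from 0.3 to 0.8; equal SD before and after; a true difference of 0.5 SD for the power illustration.

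**The plan's own figure.** "A sample of 62 participants is planned for this study", but no effect size, SD or test family is given, so 62 cannot be re-derived. Solving backwards, a two-sided t test with 41 and 21 has power 0.90 at a standardised difference of 0.88. The normal approximation agrees: (1.960 + 1.282) × √(1/41 + 1/21) = 3.242 × 0.2683 = 0.87. This serves only as a reference point; the article does not say that the trial is powered for the questionnaires.

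**Variance of the group contrast**, in units of SD² × (1/41 + 1/21):
- post scores: 1
- change scores: 2(1 − r)
- ANCOVA: 1 − r²

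ANCOVA relative to post scores is therefore 1 − r². Relative to change scores it is (1 − r²) / [2(1 − r)] = (1 + r)/2. Both are below 1 for any r between 0 and 1. The detectable difference at power 0.90 is 0.884 × √(variance); for example, ANCOVA at r = 0.6 gives 0.884 × √0.64 = 0.71.

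| Assumed r | ANCOVA / post | ANCOVA / change | Detectable: post | change | ANCOVA | Power at 0.5 SD: post | change | ANCOVA |
|---|---|---|---|---|---|---|---|---|
| 0.3 | 0.91 | 0.65 | 0.88 | 1.05 | 0.84 | 0.45 | 0.34 | 0.49 |
| 0.5 | 0.75 | 0.75 | 0.88 | 0.88 | 0.77 | 0.45 | 0.45 | 0.56 |
| 0.6 | 0.64 | 0.80 | 0.88 | 0.79 | 0.71 | 0.45 | 0.54 | 0.63 |
| 0.7 | 0.51 | 0.85 | 0.88 | 0.69 | 0.63 | 0.45 | 0.66 | 0.73 |
| 0.8 | 0.36 | 0.90 | 0.88 | 0.56 | 0.53 | 0.45 | 0.83 | 0.86 |

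These are large-sample ratios. Estimating three covariate slopes with 62 participants inflates the ANCOVA variance by about 1 + 3/(62 − 3 − 3) = 1.05, before any gain from age and gender. The least favourable entries become 0.91 × 1.054 = 0.96 and 0.90 × 1.054 = 0.95, still below 1.

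**The switch.** The rule was simulated under no group difference with 41 and 21 participants, 6000 runs per distribution. The t test was used only if Shapiro-Wilk passed in both arms, which is an assumed reading of the rule. Type I error was 5.0% for normal data, 4.9% for exponential data and 5.4% for a bounded 4-item score like PACES-S. The t test was selected in 90% of normal samples, 9% of bounded-score samples and 0.1% of exponential samples. The error rate holds, but the reported effect measure changes with the data.

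**Imputation.** Rubin's rules combine an estimate and its standard error across imputed data sets. The t test's mean difference supplies both. Mann-Whitney U as usually reported supplies a statistic and a P value, so a further step is needed.

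**The case against.** The strongest reply is that nothing here is invalid. Under randomisation an unadjusted comparison is unbiased, type I error stays near 5%, these are secondary end points, and a condensed article may leave covariates and pooling rules to an analysis plan. Most of that stands, and it limits the point to precision and interpretability. It does not remove the point: the article names the tests and the rule for choosing between them, so a later plan would have to replace that text and not merely add detail.

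Three stronger readings are tempting and not supported.

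- A reader might infer that the baseline is thrown away. That is so only if post scores are compared. Measurement before and after makes a change-score comparison an equally natural reading; it uses the baseline, though less efficiently than ANCOVA.
- A reader might infer that the planned tests cannot be combined with multiple imputation. The t-test mean difference pools by Rubin's rules. Even for Mann-Whitney U, the probability that one arm exceeds the other can be estimated with a variance. The rank test is less direct, not unusable.
- A reader might infer that different imputed data sets will lead to different tests. In simulation, running Shapiro-Wilk on each of 20 imputed data sets gave conflicting choices in 28% to 45% of runs with normal data and 54% to 68% with bounded scores (10% and 20% missing, assumed). The article does not say that the check is repeated per imputation; checking the observed data once fits the text as well.

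The gain also depends on r. At r = 0.3 it is only 9% of variance against post scores, and at r = 0.8 only 10% against change scores.

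**Conclusion.** The point holds as one of efficiency and of an effect measure left to the data, for self-efficacy, quality of life and enjoyment of physical activity. Whichever quantity is compared, the named tests are less precise than a baseline-adjusted analysis. The reduction in variance from ANCOVA is 9% to 64% against post scores and 10% to 35% against change scores over r = 0.3 to 0.8. These figures rest on assumed correlations and on equal variances before and after. There is no material effect on type I error, and the linear mixed model for step count is unaffected. It is a modest improvement that is worth making because the data needed are already planned.

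**What to change.** Replace the sentence on the three questionnaires in Statistical Methods. For KINDL, activity-related self-efficacy and PACES-S, prespecify ANCOVA of the post score on arm, baseline score, age and gender. Report the adjusted mean difference with a 95% CI, pooled over imputations by Rubin's rules. Drop the choice of test by normality; keep robust standard errors or a bootstrap CI as a sensitivity analysis. 

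The cost is one paragraph, with no extra data or visits. The article's Results section reports data collection for phase I only, so as of that text the change can be made before phase II data exist.

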## Results

Once the phase-I evaluation is completed, the outcomes will be discussed with the app development team and adjustments will be incorporated in KIJANI through this feedback loop. Data collection for the phase-I evaluation started in August 2023 and recruitment is currently still ongoing.

## Discussion

### Principal Findings

KIJANI is a mobile game explicitly developed for PA promotion in children and adolescents with a special focus on creativity as well as PA in the outdoor setting. The objective of the KIJANI intervention is to increase everyday PA in adolescents through a digital intervention approach using gamification and augmented reality. This study protocol describes the KIJANI intervention in detail, as well as the evaluation approach.

Even though activity promotion is highly indicated in adolescents, this young target group is difficult to reach, and adherence to intervention approaches, especially over the long term, is mostly rather low [22].

Several previous studies have assessed the effectiveness of mobile health approaches to increase PA in healthy adolescents. A systematic review on the effects of mobile health to increase PA concluded that mobile devices and apps may be an effective strategy for promoting PA in adolescents as they have high technology use. However, overall, there is only a small number of studies; a lack of RCTs; and a high risk of bias in this research sector, mostly including self-reported measures with the risk for recall as well as report bias [23]. Another systematic review on the quality and features of apps to improve PA, sedentary behavior, and diet also reported that generally, very few apps are available that specifically target children and adolescents and app quality was only moderate [24]. Overall, there is a need for high-quality app-based activity promotion approaches especially in children and adolescents.

Some previous studies have assessed the effects of digital gamification approaches on activity promotion. A meta-analysis revealed that the popular mobile augmented reality game “Pokémon Go” was associated with a significant increase in the users’ daily step count. In the game, participants are required to travel to different locations to capture virtual characters. Even though the game was not primarily designed to promote PA, it has reached masses of users and has shown to have the potential to influence their health behavior at least in the short term [25]. Long-term results are rare, but it seems that the novelty effect tends to wear off with time, and after 3 months, 80% of players stopped using the app [26].

Direito et al [27] assessed the effect of 2 smartphone apps, 1 immersive and 1 nonimmersive app, on cardiorespiratory fitness and PA levels in healthy young people. Both apps consisted of 8-week training programs, whereby in the immersive app the training program was embedded with a story where the user has to collect supplies and protect a town from zombies. After 8 weeks, they were not able to report any intervention effect compared with a CG in both apps. Adherence to app use was a major concern during their investigation [27].

Garde et al [28] evaluated another smartphone app called “MobileKids Monster Manor,” in which behavioral psychology, positive peer pressure, and rewards are used with a monster character theme to increase PA in healthy adolescents. In a school-based environment, this intervention increased PA over a short-term period [28].

